**Synopsis:**

Based on a wealth of research demonstrating the associations between physical health and psychosocial well-being, modern health care in the United States is characterized by an increasingly patient-centered model of care that places a premium on the holistic treatment of the patient as a physical, psychosocial, and spiritual whole. Hospital chaplains play a vital role in delivering emotional and spiritual care to a broad range of both religious and non-religious patients for a wide variety of stressors, and extensive research indicates that spiritual consults impact patient outcomes and satisfaction. However, there is remarkably little research on the “active ingredients” of chaplaincy spiritual care, and a subsequent lack of standardization and best-practice guidelines informing chaplain training and chaplain spiritual consulting. CBCT ® (Cognitively-Based Compassion Training) is a secularized compassion meditation program adapted from the Tibetan Buddhist mind training (lojong) tradition, and it may be an ideal addendum to both chaplain training programs and to the spiritual care consults provided by Emory University hospital chaplains to approximately 100,000 patients each year. Here we propose a pilot study to explore the feasibility and impact of incorporating CBCT into the educational curriculum for chaplain residents. To this end, we will (1) examine the impact of CBCT on burnout, compassion, and empathic accuracy among chaplains in training, (2) explore whether the impact persists through the end of the resident training, (3) evaluate the timing of the training within the existing curriculum to maximize its impact, (4) evaluate whether CBCT-informed interventions improve patient outcomes, and (5) explore chaplain and patient mediators of the impact of spiritual care consults on patient outcomes. Data acquired in this pilot study will be used to estimate efficacy and to inform a randomized controlled trial.

1. **Background**

[figure not shown]
Previous research indicates that CBCT (Cognitively-Based Compassion Training) improves empathic accuracy[^1^](#_ENREF_1) (Figure 1), enhances well-being[^2^](#_ENREF_2)^,^[^3^](#_ENREF_3), and attenuates the pro-inflammatory response to psychosocial stress[^4^](#_ENREF_4)^,^[^5^](#_ENREF_5) (Figure 2). CBCT is a secularized compassion meditation program adapted from the Tibetan Buddhist mind training (*lojong)* tradition, and it may be an ideal addendum to the spiritual caregiving provided by Emory University hospital chaplain residents to approximately thousands of patients each year.

Chaplains are exposed to a great deal of suffering when they provide spiritual care to hospitalized patients and their families. Chaplain residents, who are typically in their first full year of exposure to hospital chaplaincy, can be particularly impacted by the suffering to which they bear witness[^6^](#_ENREF_6). CBCT is anticipated to improve empathic accuracy and resilience in the face of suffering among chaplain residents. The compassion component of CBCT will help the chaplain develop and practice skills of compassion while the cognitive component of CBCT enhances emotional regulation and allows the chaplain to avoid becoming overwhelmed by empathic connection in the presence of another’s suffering. This allows for a compassionate response in which the chaplain is able to “hover in a sweet spot, empathic but not over-aroused.”[^7^](#_ENREF_7) If CBCT is shown to provide long-lasting benefit to chaplain residents, then the chaplaincy field as a whole will have a powerful new tool for the health and retention of healthcare chaplains.

The Emory University Spiritual Health department will incorporate CBCT into their training curriculum using a phased approach beginning in Fall 2017, which provides the opportunity to compare students receiving the CBCT addendum with those receiving traditional chaplaincy training. Here we propose a naturalistic study that examines the impact of incorporating CBCT into Emory’s spiritual caregiver training program. To this end, we will examine the effect of CBCT on empathic accuracy and resilience by comparing the first group of students who receive CBCT-informed training with chaplains who receive standard training in spiritual caregiving and receive CBCT later in the residency year. Data on empathic accuracy will be collected using an existing validated task that measures the degree of correspondence between chaplain-reported emotional states of individuals relaying illness-related experience on video and the emotional states reported by the individuals themselves at the time of video recording[^8^](#_ENREF_8). Data on chaplain resilience will be collected using self-report questionnaires measuring compassion fatigue, compassion satisfaction, empathy, anxiety, and depression.

**a. Specific Aims**

**Specific Aim 1: To estimate the effect of receiving CBCT on empathic accuracy and resilience among chaplain residents providing spiritual care to hospitalized patients.**

We will conduct a naturalistic study of up to 30 chaplain residents serving the Spiritual Health department of Emory Healthcare, and who will receive CBCT during the first unit of their year-long residency (the early-start group) or approximately midway through the residency year (the delayed-start group). Empathic accuracy and resilience will be measured for all participants before the early-start group receives CBCT (baseline, or T0); after the early-start group completes CBCT (T1); before the delayed-start group receives CBCT (T2), and after the delayed-start group completes CBCT (T3). See **Figure 3** for study schematic. The change in mean score of empathic accuracy and resilience measures from T0 to T1 among participants in the early-start group will be compared to the change in mean score among participants in the delayed-start group over the same time period.

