**2. Design**

1. **Sample:**

Emory Healthcare chaplain residents will be asked to view the empathic accuracy video scenarios and complete questionnaires at four time points during the residency year. Chaplains will be asked to wear ambulatory recording devices that record chaplain-patient interactions.

Emory Healthcare patients will be asked to complete self-report assessments before and after their Spiritual Health consult. Patients will be informed of chaplains use of ambulatory recording device for research purposes.

No children, prisoners or other vulnerable populations will be included in this study.

*Inclusion Criteria*: Chaplain residents with Spiritual Health at Emory Healthcare or patient of Emory Healthcare.

*Exclusion Criteria*: None

b. **Setting:**

Consenting chaplains will view the empathic accuracy videos and complete the study questionnaires at one or more of the Emory Healthcare campuses (EUH, EUHM, Saint Joseph’s, Emory Johns Creek, and Wesley Woods).

Consenting patients will complete self-report assesments and spiritual health consults at one or more of the Emory Healthcare campuses (EUH, EUHM, Saint Joseph’s, Emory Johns Creek, and Wesley Woods).

c. **Recruitment:**

Chaplain residents and Emory Healthcare patients will be approached in person at the Emory Healthcare campuses by a researcher and will provide written consent.

d. **Procedures**:

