During their training program, chaplain residents will provide spiritual consults to patients throughout the Emory hospital system. We will examine whether patient (n = 300) outcomes are improved for those receiving chaplain spiritual care augmented by CBCT, in comparison to those receiving spiritual care from chaplains who receive CBCT at the end of their residency program. To this end, study personnel will shadow chaplain residents in both groups and will administer self-report assessments of negative symptomology (depression, anxiety, and loneliness) and well-being (quality of life, hope) to consented patients. In addition, study personnel will audio record chaplain-patient interactions. Patient outcomes will be gathered from retrospective chart reviews and will include use of opioid pain medication, duration of stay, patient’s denial of care, and patients’ Press Ganey satisfaction scores.

In a final step, using patient chart reviews we will examine chaplain and patient factors that may mediate the link between spiritual consults and improved patient outcomes. Specifically, we will examine whether chaplain empathic accuracy or self-reported compassion mediate the impact of spiritual care consults on patient health outcomes. We will also examine whether patients’ well-being (hope, quality of life), or negative symptoms (depression, anxiety, loneliness) mediate the impact of spiritual care consults on patient health outcomes.

We will also use the ambulatory ambulatory audio recordings of the chaplain-patient interactions to interrogate which aspects of the chaplain-patient interaction mediate improved patient outcomes (see Figure 4). Spiritual consult audio recordings will be coded by 2 trained, independent CBCT instructors for CBCT content. They will also be coded for linguistic and behavioral elements derived from existing models of compassionate interaction in the hospital environment[^9^](#_ENREF_9).

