To evaluate whether CBCT-informed interventions improve patient outcomes, descriptive statistics (means, standard deviation, standard error) will be used to characterize baseline demographics and responses to self-report assessments. All data will be evaluated for normality, and appropriate procedures will be performed in cases where normality is violated. To evaluate whether CBCT-informed spiritual consults impact patients’ negative symptoms, well-being, and patient health outcomes (duration of stay and patients’ Press Ganey satisfaction scores) we will conduct independent samples t-tests. Dichotomous variables (denial of treatment, opioid use) will be evaluated using chi square tests.

To explore chaplain and patient mediators of the impact of spiritual care consults on patient outcomes, chaplain resident, patient, and chaplain-patient interactions will be tested in mediation analyses using linear regression analysis in order to examine which factors account for improvement in patient outcomes (opioid use, duration of stay, denial of care, patient satisfaction). Any chaplain variables (empathic accuracy or self-reported compassion) that are impacted by CBCT, or patient variables (negative symptoms, well-being) that are impacted by CBCT-informed modules will be entered as independent variables into linear regression analysis with group assignment, and with patient health outcomes as the dependent variable in order to examine whether chaplain, patient, or chaplain-patient interaction variables render group assignment insignificant in accounting for variance in patient health outcomes[^31^](#_ENREF_31).

1. **Compensation:**

No compensation will be provided to participants.

1. **Risks to participation:**

Chaplain residents and Emory Healthcare patients may experience some emotional discomfort while completing the questionnaires. To minimize this risk, all participants will be informed that they are free to skip any questions that are upsetting and that they can stop the questions at any time. In addition, they will be provided help in contacting the Emory Faculty and Staff Assistance Program (FSAP).

In addition, the questionnaires that subjects will fill out as part of this study will contain personal information, and participants may have private pieces of audio recorded.

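### Aim 4 compares chart outcomes between non-randomised chaplain groups across five campuses using tests that cannot adjust for campus

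*Protocol*

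**What the plan says.** **How the groups arise.** Specific Aim 1 (Protocol, a. Specific Aims) states: "We will conduct a naturalistic study of up to 30 chaplain residents serving the Spiritual Health department of Emory Healthcare". The Background says that the department brings in CBCT "using a phased approach beginning in Fall 2017" and that the study works by "comparing the first group of students who receive CBCT-informed training with chaplains who receive standard training in spiritual caregiving", the latter receiving CBCT later in the year. The Protocol states no randomisation, matching, stratification or other rule for who starts early. The Synopsis places a randomised trial after this study: "Data acquired in this pilot study will be used to estimate efficacy and to inform a randomized controlled trial".

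**Who the patients are.** Under 2. Design, any Emory Healthcare patient is eligible and no exclusion criteria are listed. The Setting paragraph has patients assessed and seen "at one or more of the Emory Healthcare campuses (EUH, EUHM, Saint Joseph’s, Emory Johns Creek, and Wesley Woods".

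**What is compared.** The Procedures paragraph states: "We will examine whether patient (n = 300) outcomes are improved", contrasting patients by their chaplain's group. Opioid use, duration of stay, denial of care and Press Ganey satisfaction come from retrospective chart review.

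**How it is compared.** The Data analysis section fixes the method for the continuous chart outcomes: "duration of stay and patients’ Press Ganey satisfaction scores) we will conduct independent samples t-tests". Opioid use and denial of treatment get chi-square tests. Baseline demographics are described but enter no test. The mediation regressions in the same section contain group assignment and candidate mediators, with no campus term.

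**The concern.** The patient comparison asks whether CBCT-informed care improves outcomes, which is a causal question. The groups are not formed by chance, and nothing in the design makes the two sets of patients alike in where they were treated. A two-sample t-test or a chi-square test attributes the whole difference between groups to the group. If early-start residents happen to see more of their patients at some campuses than delayed-start residents do, and those campuses differ in stay, opioid use, denial of care or satisfaction, that difference enters the CBCT estimate.

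This is a bias in the point estimate. It could create an apparent effect or hide a real one, and a larger sample would not remove it. It is also distinct from the clustering of patients within chaplains, which concerns the standard error. At stake is the efficacy estimate that the Synopsis intends to carry forward into planning a randomised trial.

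**Working it through.** The Protocol gives no effect size, SD, significance level, power or split by group for the 300 patients, so there is no stated figure to reproduce. What follows shows only how the bias would behave.

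**Inputs from the Protocol:** 300 patients; up to 30 residents; five campuses.

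**Assumptions not in the Protocol:** 150 patients per group (300 / 2); two-sided significance level 0.05; two campus types; within-campus SD of 1; patients independent; true CBCT effect zero.

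**Step 1: bias.** Let s_E and s_D be the shares of early-start and delayed-start patients at campus type A, and D the difference in mean outcome between types A and B. The expected unadjusted difference between groups is

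bias = (s_E − s_D) × D.

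For shares of 70% and 30% and D = 0.3 SD: (0.70 − 0.30) × 0.3 = 0.12 SD. For equal shares: 0 × D = 0.

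**Step 2: effect on the t-test.** The standard error is sqrt(2/150) = 0.115 SD. The chance of a significant result with no CBCT effect is Φ(bias/SE − 1.96) + Φ(−bias/SE − 1.96).

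| Campus difference D (SD) | Gap in share (points) | Spurious difference (SD) | False-positive rate |
|---|---|---|---|
| any | 0 | 0 | 5% (nominal) |
| 0.2 | 20 | 0.04 | 6% |
| 0.3 | 20 | 0.06 | 8% |
| 0.3 | 40 | 0.12 | 18% |
| 0.5 | 40 | 0.20 | 41% |
| 0.5 | 60 | 0.30 | 74% |
| 0.5 | 100 | 0.50 | 99% |

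For scale, the smallest difference detectable with 80% power under these assumptions is (1.96 + 0.84) × 0.115 = 0.32 SD.

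**Step 3: a binary outcome.** Suppose opioid use is 60% at type A and 40% at type B. With a 40-point gap in share:
- Early-start: 0.7 × 0.60 + 0.3 × 0.40 = 54%.
- Delayed-start: 0.3 × 0.60 + 0.7 × 0.40 = 46%.

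The spurious difference is 8 percentage points and the false-positive rate is about 28%. It is about 10% at a 20-point gap and 94% at a full split.

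**Step 4: what a campus term does.** Within each campus type the expected group difference is zero, so a model with group and campus removes this bias. The price is variance. With equal groups and a 70/30 split, the correlation between group and campus is 0.70 − 0.30 = 0.40, so the variance rises by 1 / (1 − 0.40²) = 1.19 and the standard error from 0.115 to 0.115 × sqrt(1.19) = 0.126 SD. At a full split the correlation is 1, the denominator is zero, and no model can separate group from campus.

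**The case against.** **The Protocol never links start slot to campus.** This stands. No passage says which residents start early or where they work. Some text points away from a campus split: the early-start CBCT didactics are virtual, and consults are given throughout the hospital system. A reader might infer that the groups are divided by campus. The document does not support that. Confounding is possible, not shown.

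**Every magnitude is assumed.** This stands too. Neither the campus differences nor the splits are anchored in the Protocol, and with equal campus shares the bias is zero. The table shows a mechanism and a range; it does not predict the size of the error.

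**Covariates belong in a SAP, which is not shown.** This would answer a mere silence about covariates. Here the Protocol itself names the tests, and they admit no campus term.

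**A naturalistic pilot is entitled to be non-random.** This stands. A reader might infer that residents should be assigned to start slots by lot. The design openly follows a curriculum change and defers randomisation to a later trial, so non-random timing is a declared limit and not an error. The declared limit is a reason to adjust the comparison, not a reason to leave it unadjusted.

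**Other outcomes have baselines.** This stands and narrows the point. A reader might infer that Aim 1 faces the same risk. Aim 1 compares change from T0 to T1, so stable campus differences cancel and only campus-specific trends would matter. Patient self-reports are also taken before and after the consult. The four chart outcomes have no stated baseline.

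**Conclusion.** The concern holds for Aim 4's four chart outcomes: duration of stay, Press Ganey satisfaction, opioid use and denial of care. The Protocol fixes unadjusted tests for a causally worded comparison of non-randomised groups over five campuses, and nothing in it balances campus between the groups.

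The size cannot be derived from the document. Under the stated assumptions, a 0.3 SD campus difference with a 40-point gap in share gives a spurious 0.12 SD and about 18% false positives. The combinations examined run from 6% to 99%, and equal shares give no bias.

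The point does not extend to Aim 1. It does not establish that the groups differ by campus, and it makes no claim about hospital wards, which the Protocol does not name (its educational units are something else). It warrants a change to the analysis text, not a redesign of the study.

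**What to change.** In the Data analysis section:

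1. For duration of stay and Press Ganey scores, replace the independent-samples t-tests with linear models containing group and campus, where campus is the one at which the consult took place. The existing provision for non-normal data can stay.
2. For opioid use and denial of treatment, replace the chi-square tests with logistic models containing the same two terms.
3. Tabulate patients by group and campus alongside the results.
4. Report as confounded any campus staffed by one group only. Such a campus adds nothing to the within-campus comparison.

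**Cost.** Campus is known from where each consult occurs, so this should need little or no new data. Five campuses use 5 − 1 = 4 degrees of freedom. That is small against 300 patients, but group varies over at most 30 chaplains, about 30 / 5 = 6 per campus on average, so the loss of precision is larger than the patient count suggests. Adjustment for campus also leaves differences between wards within a campus untouched, and the report should say so.

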**Specific Aim 2: To evaluate whether the effect of CBCT among chaplain residents persists over the residency year.**

For participants in the early-start group only, the change in mean score of empathic accuracy and resilience measures from T0 to T1 will be compared to the change in scores over the T1 to T2 and T2 to T3 time periods..

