Participants will be approached by a researcher who will explain the study to them and have them sign an informed consent document if they understand the study component and are interested in participating. Chaplain resident participants will receive the CBCT as part of their clinical pastoral education (CPE) curriculum. Chaplain resident participants will receive the CBCT either in the first educational unit (the early-start group) or approximately midway through the residency year (the delayed-start group). Residents in the early-start group will meet virtually for a didactic approximately every two weeks to discuss their residency experience in the context of their CBCT knowledge and caregiving approach. Residents in the delayed-start group will meet for a similarly structured and scheduled didactic on spiritual health topic(s) unrelated to patient care. After the delayed-start group receives CBCT approximately midway through the residency year, the students in the delayed-start group will also meet virtually for the CBCT-focused didactic to discuss their residency experience in the CBCT context and the early-start students will receive the spiritual health didactics on topic(s) unrelated to patient care. All didactics will be 1.5 hours in length. All chaplain resident participants will view the empathic accuracy video and complete the questionnaires at four times during the residency year: before the early-start group receives CBCT (baseline, or T0); after the early-start group completes CBCT (T1); before the delayed-start group receives CBCT (T2), and after the delayed-start group completes CBCT (T3). A subset of the chaplain residents will be interviewed at three time points relative to their training in CBCT. The interviews consist of open-ended questions to further query their learning experiences with CBCT. Researchers will compare differences in the mean scores of empathic accuracy and resiliency measures over time.

[figure not shown]

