**Audio Recordings:**

Chaplain residents will wear a recording device that will record chaplain-patient interactions. Patients will be informed that they can stop the recording at any time and that they can ask for their recording to be deleted at any time if they no longer wish for it to be a part of the study. Audio recordings will be de-identified, such that patient and chaplain are only linked with participant IDs and identity will not be available to anyone coding the recordings. Patients and chaplain participants will complete an assent form to indicate how their recordings can be used, including whether recordings can be used for other research projects by our team, by other researchers, and for scientific presentation of these data.

1. **Data analysis**

We will analyze the data to test the hypothesis that CBCT improves chaplain residents’ empathic accuracy and resilience in a hospital setting. SAS 9.4 and SPSS 23 will be used to conduct statistical analysis of the collected data. Descriptive statistics will be used to describe selected characteristics of participants by group, expressed as frequencies and percentages. The primary outcomes of empathic accuracy, compassion fatigue, compassion satisfaction, empathy, anxiety, and depressive mood will be measured as pre-to-post differences in the measurement scores, i.e., T1 – T0. For the early-start group and T3 – T2 for the delayed-start group. We will examine the effect of CBCT by analyzing the correlated, repeated-measure data (T1 – T0) – (T3 – T2) using mixed linear models, implemented in SAS Proc Mixed. Mean pre-to-post differences will be compared across groups.

To evaluate whether the effects of CBCT persist over time, differences between mean scores on measures of empathic accuracy and resilience for the early-care group will be compared across four time points: from baseline measurement to early-group post-CBCT measurement (T1 – T0), from early-group post-CBCT measurement to delayed-group pre-CBCT measurement (T2 – T1)_,_ and from delayed-group pre-CBCT measurement to delayed-group post-CBCT measurement (T3 - T2). To evaluate whether the effects of CBCT depend on the timing of program delivery, the differences between mean scores on empathic accuracy and resilience will be compared for each group during the period following receipt of the CBCT program; that is, (T1 – T0) – (T3 – T2).

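### Aim 2 compares the first interval's change with the later changes, a contrast that does not measure whether the CBCT effect persisted

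*Protocol*

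**What the plan says.** Specific Aim 2 sets the question: "To evaluate whether the effect of CBCT among chaplain residents persists over the residency year". The method is restricted: "For participants in the early-start group only". Within that group, "the change in mean score of empathic accuracy and resilience measures from T0 to T1 will be compared to the change in scores over" the two later intervals, T1–T2 and T2–T3.

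The Data analysis section says that "differences between mean scores on measures of empathic accuracy and resilience for the early-care group will be compared across four time points". The quantities it then lists are three successive changes, not four levels: "from baseline measurement to early-group post-CBCT measurement (T1 – T0"), "from early-group post-CBCT measurement to delayed-group pre-CBCT measurement (T2 – T1"), and T3 – T2.

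Neither place compares T2 or T3 with T0, sets T2–T1 or T3–T1 against zero, or gives a retention margin. Specific Aim 1 and the Procedures have all residents measured at all four visits, with T2 falling before the delayed-start group receives CBCT.

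**The concern.** An effect that persists is one whose level, once gained, stays up. In terms of change, that is a gain from T0 to T1 followed by about no change. The planned comparison asks something else: whether the later changes equal the first one. A fully retained effect fails that equality, and so does a lost one.

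A reader of the results could easily take a later change smaller than the first as a sign that the effect faded. That reading is wrong exactly when the effect was kept in full. The protocol says the pilot data will be used to estimate efficacy and inform a randomised trial, so a mistaken persistence conclusion could carry forward.

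The second issue is the missing comparator. Aim 1 uses the delayed-start group to account for what happens to residents without CBCT. Aim 2 does not, although that group is still without CBCT at T2. Drift over the residency year and effects of repeating the same tasks and questionnaires can then be mistaken for persistence or decay.

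**Working it through.** **Inputs.** The contrasts come from Specific Aim 2 and Data analysis. The protocol gives no sample size, power or alpha for this aim, so there is no figure to reproduce. The algebra needs no outside number.

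**Contrasts.** C1 = (T1–T0) – (T2–T1) and C2 = (T1–T0) – (T3–T2).

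| Mean path at T0, T1, T2, T3 | C1 | C2 | T2–T1 | T3–T1 |
|---|---|---|---|---|
| Fully retained: 0, d, d, d | d | d | 0 | 0 |
| All lost by T2: 0, d, 0, 0 | d – (–d) = 2d | d | –d | –d |
| Half lost by T2, all by T3: 0, d, d/2, 0 | 1.5d | 1.5d | –d/2 | –d |
| Same gain each interval: 0, d, 2d, 3d | 0 | 0 | d | 2d |
| No effect: 0, 0, 0, 0 | 0 | 0 | 0 | 0 |

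C2 is the same for full retention and for full loss by T2. C1 is non-zero for both. The last two columns separate retention from loss.

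**Trend.** Let drift and repeat testing add g1, g2 and g3 in the three intervals, in both groups. Under full retention:
- C1 = (d + g1) – g2 = d + g1 – g2. The drift cancels only if it is equal in the two intervals, which nothing in the protocol ensures.
- Early-group T2–T1 = g2, so drift alone can look like decay or growth.
- Early minus delayed in T2–T0 = (d + g1 + g2) – (g1 + g2) = d. Shared drift is removed whatever its shape.

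**Size, on assumed values.** The protocol says only up to 30 residents and states no split. Assume 15 per group, SD 1 at each visit, the same correlation r between any two visits, and two-sided 0.05 t-tests. The variances are 6(1–r) for C1, 4(1–r) for C2 and 2(1–r) for T2–T0. At r = 0.5 the SDs are √3 = 1.73, √2 = 1.41 and 1. Simulated rejection rates (20,000 replicates) for d = 0.8:

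| Path | C1, r = 0.5 | C2, r = 0.5 | C1, r = 0.7 | C2, r = 0.7 |
|---|---|---|---|---|
| Fully retained | 38% | 53% | 58% | 75% |
| All lost by T2 | 92% | 53% | 99% | 75% |
| Same gain each interval | 5% | 5% | 5% | 5% |

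For d = 0.5 and r = 0.5, C1 rejects in 18% (retained) and 55% (lost), and C2 in 25% for both.

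**Precision of the replacement under full retention.** Within the early group, T2–T0 has non-centrality (0.8/1) × √15 = 3.10 on 14 df, which gives 82% power. The between-group difference in T2–T0 has 0.8 × √(15/2) = 2.19 on 28 df, which gives 56%. With d = 0.5 the figures are 44% and 26%. With r = 0.7 and d = 0.8 they are 96% and 78%.

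**The case against.** The strongest reply is that the protocol states no decision rule. It says only that changes will be compared, in a pilot meant for estimation. The Data analysis section names T1–T0, T2–T1 and T3–T2 separately. Read with their signs, T2–T1 near zero means retention and a negative value means loss, and T3–T1 is the sum of two listed changes. This stands in part: the information is there. It does not rescue the planned comparison, because both places name a comparison between interval changes, and neither says that a later change will be judged against zero.

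Two objections to the replacement also stand. The delayed-start group is an untrained comparator only to T2, so the rest of the year stays uncontrolled. The study is called naturalistic and no randomisation is described, so the group difference removes shared trends but not differences between the groups.

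Some stronger readings are tempting and should not be made:
- A reader might infer that Aim 2 cannot be answered from this study. The scheduled visits can inform it; the fault is in the contrast.
- A reader might infer that a null result means continued growth. It also arises with no effect at all.
- A reader might infer that loss shows as twice the effect in both later comparisons. That holds only for the interval in which the loss occurs; loss by T2 gives 2d and then d.
- A reader might infer that CBCT didactics for the early group end at T2. The Procedures place the change, when "the early-start students will receive the spiritual health didactics on topic(s) unrelated to patient care", after the delayed group's CBCT, which is not clearly T2.

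**Conclusion.** The point holds for the contrast as written in both places. That conclusion is algebraic and depends on no assumed effect size, correlation or group size: full retention gives (d, d), full loss by T2 gives (2d, d), and no effect and equal repeated gains both give (0, 0). Neither a significant nor a null comparison tells the reader whether the effect persisted.

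Leaving out the delayed-start group is a secondary weakness. Using it controls for shared trends up to T2 only.

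The rejection rates and powers are illustrations on assumed inputs. They should not be read as the study's operating characteristics.

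**What to change.** Change Specific Aim 2 and the matching paragraph of Data analysis together:

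1. Define persistence at T2 as the early-minus-delayed difference in T2–T0.
2. Report early-group T2–T1, T3–T1 and T3–T0 with confidence intervals as retention estimates. State that T3 has no untrained control and that these within-group figures include any drift over the year.
3. State that the groups are not described as randomised, so the between-group estimate may carry group differences.
4. Interpret the results alongside the didactic schedule in the Procedures: the early group attends CBCT didactics until the switch that follows the delayed group's CBCT.

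The cost is wording plus some precision: on the assumptions in the working, about 56% power for the between-group contrast against 82% for the within-group T2–T0 change. All four visits are already scheduled for both groups, so no new visits or measures are needed.
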